## Abstract

**Background:**

Calls have been made to rethink the mental health support currently available for young people. This study aims to help re-focus and reduce the inaccessibility of mental health services by offering an adapted version of a theoretically-driven, evidence-based, guided psychosocial intervention known as ‘Groups 4 Health’ (G4H). To date, the G4H intervention has mainly been trialled in Australia, with promising positive effects on social connection, mental health and well-being. The present study examines the feasibility of running a randomised controlled trial when delivering the G4H intervention for young people in the UK.

**Methods:**

The TOGETHER study is a feasibility randomised controlled trial of an adapted version of the G4H intervention. Participants are aged 16–25, currently experiencing mental health difficulties and recruited from mental health services. The target sample size is 30, with 15 in each trial arm. Participants are randomly allocated to either G4H plus treatment as usual, or treatment as usual alone. The primary outcomes of interest are the feasibility of recruitment, randomisation, data collection and retention to the study at 10 and 14 week follow up, as well as the acceptability, and accessibility of the study protocol and G4H intervention.

**Discussion:**

The results of this study will indicate if further optimisation is required to improve the feasibility, acceptability and accessibility of the intervention and study protocol procedures as perceived by end users and practitioners. This offers a significant opportunity to support the local and national demand for accessible, innovative, and effective psychosocial youth mental health support.

**Trial registration:**

ISRCTN registry (ISRCTN12505807). Registration date: 11/04/2022.

## Introduction

Severe and enduring mental health problems begin in adolescence, often emerging between the age of 15 and 25 years [1]. Despite a clear need to focus on young people’s mental health, concerns about the availability and adequacy of mental health support have risen considerably, with an increasing narrative from young people that their needs are not being met [2–4]. This is often particularly true for vulnerable young people, such as those with complex and severe mental health difficulties, unstable or inactive employment, and low socioeconomic status, who may disengage from, or may not meet the diagnostic entry thresholds for the standard NHS youth mental health services.

Calls have been made for the government to commit to a recovery plan for young people that rethinks the mental health support currently available [5]. Recommendations have been made to utilize the thousands of professionals working with young people who currently have limited or no training in psychological approaches [4]. Recommendations have also been made to implement practice innovations that directly address social isolation [6, 7]. Research has consistently shown that the presence, severity and longevity of physical and mental health problems in young people is associated, and often preceded, by increased loneliness and diminished social interactions [4, 8, 9]. In contrast, social connection and multiple group memberships are associated with improvements in mental health symptoms [10], well-being [11], and resilience [12].

Vulnerable young people have been associated with smaller social networks [13] and the presence of social disability [14]. Assisting young people to engage in social relationships and activities, may help to prevent the onset and longevity of severe mental illness, as well as reduce the use of mental health services over time [14–16]. Addressing the underlying social causes of mental ill health is now also particularly pertinent following the prolonged social restrictions enforced to control the spread of the COVID-19 virus [17, 18]. It is evident that young people with complex needs, i.e. co-present mental health and social difficulties, when they can access services, receive varying packages of support within a complex landscape of youth and mental health services [19]. The provision of interventions focused on social factors is variable and often poor. Services often aim to focus on diagnostic remission, symptom reduction, or a narrow promotion on paid employment. Such approaches do not always well match the typical heterogeneity of youth mental health presentations, nor necessarily what is most meaningful to young people themselves [20]. Services supporting youth mental health should aim to strengthen resilience in social and existential (i.e. life meaning) domains, and serve the higher-order processes of social participation and recovery [20].

This study aims to address the urgent need to re-focus youth mental health support towards enhancing social connection. It also aims to help reduce the inaccessibility and burden on mental health services by offering an evidence-based psychosocial intervention, known as ‘Groups 4 Health’ (G4H) [21], to clinical, health and community youth services. G4H is a modularised, guided psychosocial intervention that does not require extensive training to use. The intervention is built on the social identity approach to health, which proposes that positive social identities (identities based on beneficial group memberships) provide the psychological resources necessary to promote and maintain good physical and mental health [22]. G4H targets social connection and loneliness (through group-based belonging) with concomitant benefits for mental health and well-being [23, 24].

Trials so far have shown that the G4H intervention is associated with improvements in social connectedness, depression, anxiety, stress and life satisfaction for young people and adults from clinical, student and general population samples who are experiencing loneliness or low mood through an increase in positive social identities [21]. Trials have also indicated that loneliness is reduced considerably more when participants have received the G4H intervention, than compared to a matched no-treatment control group, a treatment as usual group, and group cognitive behavioural therapy [23–25].

To date, the G4H intervention has mainly been trialled in Australia, using a group-based delivery format. The recruited samples also tend to be adults, who meet the criteria for clinical symptoms of depression. Only one registered study has focused on the G4H intervention in the UK, and this study similarly focuses on the adaptation of the intervention for adults accessing treatment for depression in secondary care services. Questions therefore remain about the transferability of the intervention to, not just young people in UK based services, but also vulnerable young people with complex mental health and support needs. Based on the research team’s extensive experience of working on trials with young people with complex social and mental health needs, as well as a recent consultation with a specialist children and young people’s mental health service, it is considered that the intervention may be more accessible to vulnerable young people when delivered individually. Further research is now needed to understand the feasibility, accessibility and acceptability of the intervention when delivered in this way. In the context of a complex youth mental health service landscape, there is a need to better understand what types of services could feasibly deliver a brief manualised social groups and connectedness intervention, and in what types of services this intervention may be effective. Moreover, the recommendations to utilise professionals with limited or no training in psychological approaches to augment youth mental health service provision [4] does not necessarily mean that these professionals want to or will deliver the type of intervention being tested in this study. Thus, there is a need to explore the mechanisms and contextual factors that may affect the future uptake and implementation of the intervention, in both research and clinical contexts.

The present study will be the first known to examine the feasibility of delivering the G4H intervention with vulnerable young people in UK based community, health and youth mental health services. This study will also examine the feasibility parameters related to the design of a randomised controlled trial, in such UK based services. The results will indicate if further optimisation or adaptations are required to improve the feasibility, acceptability and accessibility of the intervention and study protocol procedures, as perceived by end users and (actual and potential) intervention providers. Findings will also provide valuable information from actual and potential intervention providers regarding their perspectives around intervention implementation. This will inform the overarching intervention implementation strategy, ensuring too that future research studies accurately reflect this intended end deployment. This study offers a significant opportunity to better meet the local and national demand for accessible, innovative, and effective youth mental health support.

### Aims

The project aims to evaluate the feasibility, acceptability and accessibility of a randomised controlled trial delivering an adapted social connection intervention (Groups 4 Health; G4H) to young adult service-users who are currently experiencing mental health difficulties.

### Primary research questions

1) Is it feasible to conduct a randomised controlled trial for the G4H intervention when delivered to young service-users accessing community, health and/or youth mental health services?2) Is the G4H intervention feasible to deliver to young service-users involved in community, health and/or youth mental health services?3) Is the G4H intervention safe and acceptable according to both the young service-users receiving the intervention, and the practitioners delivering the intervention?4) What changes are indicated to improve the safety, acceptability, accessibility and feasibility of the intervention?

### Secondary research questions

5) What is the most suitable primary outcome for a future larger trial of the G4H intervention?6) What are the attitudes, experiences and contextual factors relevant to the implementation of an intervention for social connectedness by practitioners’ working with young people with mental health problems?7) What are young people’s experiences and perceptions of the benefits and harm of identification with online-based social groups?

## Methods

### Trial design

TOGETHER is a single-blind, parallel-group feasibility randomised controlled trial, and a multi-site single time-point online practitioner implementation survey. Participants aged 16–25 who are currently experiencing mental health difficulties will be independently randomised to receive either an adapted version of the G4H intervention alongside treatment as usual, or treatment as usual only. The trial will run in the context of community, health and/or youth mental health service settings in the South East of England. The practitioner implementation survey will run in service settings nationally. The CONSORT (Consolidated Standards of Reporting Trials) Statement and CONSORT Checklists will be used to report the trial. For this protocol, the SPIRIT (Standard Protocol Items: Recommendations for Interventional Trials) Figure and Checklist are provided (see S1 File).

### Participants

The study will recruit trial young adult participants, intervention providers and practitioner survey respondents. See S2 File. for the eligibility criteria to take part as an intervention provider and practitioner survey respondent. The trial aims to recruit 30 young adult participants, providing 15 participants in each trial arm.

### Inclusion criteria

Aged 16–25 years oldAccessing a community, health and/or youth mental health service involved in the studyBe experiencing current mental health difficulties (operationalised by a rating of 60 or below on the Global Assessment Scale [GAS])Able to read, write and speak in English/ OR are non-English speaking but have access to an interpreter; to the degree they can give informed consent, are able to fully understand and participate in both the assessment questions and intervention content

### Exclusion criteria

Be at immediate and serious risk to self or others (assessed at the point of referral/eligibility review)Be currently participating, or be confirmed to participate in another interventional research study in which they are receiving an intervention that targets social isolation or utilises psychological therapyBe expected to be discharged, or be known to be unable to seek support from the referring service, in the 16 weeks following a referral to the trial being made (14-week research involvement + 2 weeks allowing for any missed/rearranged meetings)

### Intervention

#### G4H

The intervention is G4H plus TAU. G4H is a theoretically driven, evidence-based, manualised intervention designed to improve social connection and well-being through facilitating integration to social groups [26]. The intervention is delivered via five sessions, each taking approximately 60 to 90 minutes. The first four sessions are delivered weekly, and the final session is delivered one month later. The G4H sessions are supplemented with a workbook, offering a summary of the main learning points and space to complete activities. The five sessions aim to: raise awareness of the value and benefits of groups for health; develop a social map to identify existing connections and possible areas for social growth; train skills to maintain and use existing networks, and/or reconnect with valued groups; explore if existing connections reflect the important aspects of the self, and create an action plan; reinforce key messages and troubleshoot any problems experienced with implementing the developed social action plan.

The G4H intervention is delivered by trained intervention providers who are either working in the services who have agreed to be involved in the trial or are associated members of the research team with relevant experience. Following consultation with practitioners and young people, the trial offers an adapted version of G4H (see Patient and Public Involvement section). For this study, the sessions are typically delivered in a 1:1 format, with the option to take part in sessions as a group. The intervention sessions are held either online or in-person; allowing services to follow their usual policies and/or procedures for contact with service-users.

#### TAU

The control comparator is treatment as usual. This consists of any support, medication or interventions that participants may be receiving from any statutory or non-statutory public services and/or private services.

#### Intervention training & adherence

Those who have consented to be intervention providers in the study are invited to a group training session delivered by a member of the Groups 4 Health team. The training session may be held in-person or online using videoconferencing facilities. Intervention providers are provided with a copy of the intervention manual and workbook and asked to follow the detailed intervention manual where possible. For each delivered session of the intervention, intervention providers are asked to complete an intervention adherence form. Questions relating to perceived fidelity to the intervention, and perceived barriers to maintain fidelity to the intervention are asked in a semi-structured interview with intervention providers.

### Outcomes

#### Primary outcomes

The primary outcomes of interest are:

Number of potential service-user participants referredNumber of intervention providers who consent to take partNumber and proportion of referred potential service-user participants who consent to take part in the studyNumber and proportion of referred potential service-user participants found to be eligibleNumber and proportion of consenting eligible participants who are retained in the study at post-intervention (10 week follow up) and until the last time point (14-week follow up)Number and proportion of survey measures completed by each participant for each time-pointNumber and proportion of consenting eligible service-user participants who take part in all five G4H sessionsNumber and proportion of intervention adherence components completed for each session and across the whole G4H interventionNumber and nature of adverse events experienced by study participantsNumber and proportion of breaks in blinding

The key feasibility parameters for the study include:

≥ 50% of referred potential participants will be found to be eligible≥ 80% of consenting eligible participants will be retained in the study at each follow up time point≥ 80% data completeness≥ 80% of participants allocated to receive G4H will complete at least four sessions≥ 80% of the core G4H intervention items will be delivered

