**Fig 1 pone.0288676.g001:**
[figure not shown]
Standard Protocol Items: Recommendations for Interventional Trials (SPIRIT); schedule of enrolment, interventions and assessments.

All trial participants are invited to complete a semi-structured interview (either post 10 week follow up assessment or post intervention delivery, as relevant to the type of participant). Verbal consent to be audio-recorded is obtained. Across the trial, all personal information and research data is collected online, on a day and a time suitable for the participant; either independently or with a researcher in-person or via telephone or email. If required, a member of the research team may read study documents to the individual, and/or record participant responses on their behalf (with participant permission).

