#### Adverse events

All adverse events will be categorised and recorded from the point of randomisation until completion of the final follow up assessment for young adult participants, and from the point of informed consent until post-intervention interview for intervention providers. All serious adverse events, and suspected, unexpected, serious adverse reactions (SUSARs) will be reported to study sponsor and NHS research ethics committee as appropriate.

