### Sample size

The trial aims to recruit 30 young adult participants, providing 15 participants in each trial arm. The target sample size exceeds the recommended minimum sample size for feasibility studies [29], and a power calculation was not undertaken as the study focus is on feasibility goals and not the statistical significance of treatment effects [30]. Similarly, the sample size of intervention providers is not pre-determined and is dependent on the number of eligible practitioners in each of the services involved in this study. This feasibility study aims to monitor the number of intervention providers who consent to take part to inform the design of a larger RCT study. The study will also recruit a minimum of 100 survey respondents from UK services involved in supporting young people aged 16–25 to complete the practitioner implementation survey.

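### The primary safety outcome counts adverse events rather than people and does not name its population, so it cannot show how many young people were affected in each arm

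*Protocol article*

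**What the plan says.** The Primary outcomes list in the protocol article contains one safety item: the number and "nature of adverse events experienced by study" participants. Several neighbouring items are person-based. Consent, eligibility, retention and session attendance are each to be given as a number and a proportion of people, and most of these specify service-users. The safety item does neither.

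The Adverse events section sets two recording windows. For young people, events are "recorded from the point of randomisation until completion of the final follow up assessment for young adult participants". For those delivering G4H, they are recorded "from the point of informed consent until post-intervention interview for intervention providers".

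The Participants section states: "The study will recruit trial young adult participants, intervention providers and practitioner survey respondents". The text after Fig 1 says that all trial participants are invited to interview, "either post 10 week follow up assessment or post intervention delivery, as relevant to the type of participant", so there the word covers more than one kind of person.

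On numbers, Sample size says "The trial aims to recruit 30 young adult participants, providing 15 participants in each trial arm", while "the sample size of intervention providers is not pre-determined". Primary research question 3 asks: "Is the G4H intervention safe and acceptable according to both the young service-users receiving the intervention, and the practitioners delivering the intervention".

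**The concern.** There are two weaknesses in how the outcome is fixed.

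**Unit.** A total of events does not say how many people had one. Describing the nature of the events gives their type, not how they are spread over people. Entry requires a Global Assessment Scale rating of 60 or below, so repeated events in one young person are plausible. In an arm of 15, that person could supply most of the total. The reverse also holds: a modest total could conceal that several different people were affected.

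**Population.** The item says study participants without defining them, and events are collected from two groups. Providers are not randomised, deliver only G4H, have their own window and have no fixed number. Their events have no counterpart in the control arm. A reader of the results needs to know whether they are in the count.

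At stake is the numerical part of the answer to research question 3, and what a larger trial would take from it about the proportion of young people who have an event.

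**Working it through.** **Plan's own figures.** The article gives no adverse-event rate, threshold, test or power figure, so there is no safety figure to reproduce. The one relevant sum, 15 × 2 = 30, agrees with the stated sample size.

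**Step 1: what an event count leaves open.** Input from the article: 15 young people per arm. Assumed: six events in one arm. Proportion affected = people with at least one event / 15, with exact (Clopper-Pearson) 95% intervals.

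- One person with six events: 1/15 = 6.7% (0.2% to 31.9%).
- Six people with one event each: 6/15 = 40% (16.3% to 67.7%).

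The outcome as worded is six in both cases.

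**Step 2: share of an arm's total from one person.** Share = k / (k + events in the others). With k = 6 and the others having 0, 2 or 4 events in all, the share is 6/6 = 100%, 6/8 = 75% or 6/10 = 60%.

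**Step 3: stability by chance alone.** 200,000 simulated trials per setting, 15 per arm, the same true rate in both arms. Counts are gamma-Poisson (negative binomial with dispersion k; smaller k means more clustering within people). The table gives the probability that the larger arm figure is at least twice the smaller.

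| Mean events per person | Clustering | Event totals | People with at least one event |
|---|---|---|---|
| 1 | k = 0.5 | 32% | 17% |
| 2 | k = 0.5 | 26% | 7% |
| 1 | k = 1 | 22% | 10% |
| 2 | k = 1 | 14% | 2% |
| 1 | none (Poisson) | 8% | 3% |
| 0.3 | k = 0.5 | 52% | 46% |

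The person count is steadier in every row, but by little when events are rare. The means, the values of k and the 2:1 criterion are all assumptions. The article supplies none of them, so the table is an illustration and not an estimate for this trial.

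**Step 4: provider events, if they were pooled.** Assumed: 3 to 10 providers, 0.1 to 0.2 events each, and 3 events among young people (15 × 0.2). Provider share = provider events / (provider events + 3).

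- Low end: 3 × 0.1 = 0.3, and 0.3/3.3 = 9%.
- High end: 10 × 0.2 = 2, and 2/5 = 40%.

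**Step 5: does the text settle the population?** The Adverse events section names young adult participants and providers separately, which points to separate handling. The interview text uses participant for both kinds of person, and the safety item drops the service-user qualifier that nearby items carry. Taken together, these passages neither include nor exclude providers.

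**The case against.** The strongest reply is that nothing in the article is wrong. Number and nature is a valid description of adverse events, and events are to be categorised. A listing for 30 young people would probably reveal repeated events in one person. Breakdowns by person, arm and seriousness are usually specified in a full protocol or analysis plan, and neither is shown here. The Data management section says that research data carry a unique participant number, so a count of people could be made at analysis whatever the outcome says. Much of this stands, and it is why the point is minor. It does not remove the point, because the article fixes the unit of a primary outcome, and that unit does not call for a count of people.

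A reader might infer two stronger claims, which the article does not support:

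- *That provider events will be added to the count or to the G4H arm.* Pooling is nowhere stated, the two groups have separate windows, and collecting provider events is reasonable because research question 3 also asks for the practitioners' view.
- *That one person, or provider events, could decide the safety result.* None of the key feasibility parameters concerns adverse events, the Analysis section is descriptive, and safety is also examined through qualitative data from young people and providers. There is no numerical safety verdict to tip. One person can dominate the reported count, and no more than that.

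The simulated imbalances are also open to challenge. The 2:1 rule is not the trial's, and the person count itself crosses it in 17% of trials at a mean of 1 and k = 0.5, so part of the instability comes simply from having 15 per arm.

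**Conclusion.** The point holds as a minor one. The only quantitative safety outcome listed counts events in an undefined population. Read literally, it cannot distinguish 6.7% from 40% of an arm affected when six events are reported, and it leaves open whether provider events are counted. The first conclusion rests only on the wording and on 15 per arm; the six events are an assumed example. The simulated figures and the 9% to 40% provider share depend on assumed rates, clustering and provider numbers, and they show direction only. No figure in the article changes.

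**What to change.** Keep the listing of the number and nature of events. Add to the outcome: the number and proportion of randomised young people with at least one adverse event, and with at least one serious adverse event, by arm, with all randomised as denominator. State that this outcome concerns the randomised young people, and report intervention-provider events in a separate table covering their own window, not added to either arm.

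The cost is a change of wording and one extra table. No new data collection should be needed, provided each event record carries the participant number that the Data management section describes.

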#### Recruitment and procedure

The trial will run in the context of community, health and/or youth mental health service settings in the South East of England. The study aims to include: the Sussex Partnership NHS Foundation Trust Children and Adolescent’s Assertive Outreach Team; a Sussex, Kent or Surrey based Primary Care service; a Sussex-based YMCA youth advice centre or residential service. The practitioner implementation survey will be open to NHS and non-NHS services across the UK.

To recruit young adult participants, all organisations who have agreed to be involved in the trial are provided with the young adult-focused participant information sheet, study information video (with video transcript), study poster, referral information sheet and referral form. The involved organisations are asked to discuss the study opportunity and/or share the study documents with potential eligible young people. Potential participants who are interested and provide verbal permission to be contacted by the researcher, are referred by the involved organisation. Researchers then invite potential participants to provide informed consent and to be screened for study eligibility. Eligible participants are then invited to complete the baseline assessment and, upon doing so, are randomised. All randomised participants are invited to complete two post-allocation follow up assessments at 10 and 14 weeks. Participants receive £20 in vouchers (£60 in total) for each assessment time point. Please refer to Fig 1 (SPIRIT figure) for the schedule of enrolment, allocation, intervention and assessments. For information about the recruitment and consent process for intervention providers and practitioner survey respondents, see S2 File.

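### The 80% retention parameter is set on consenting eligible participants, but only randomised participants are followed up, so loss before randomisation counts as non-retention

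*Protocol article*

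**What the plan says.** The list of key feasibility parameters under Primary outcomes asks that at least "80% of consenting eligible participants will be retained in the study at each follow up time point". The primary outcome that this threshold judges, retention at 10 and 14 weeks, is also expressed as a proportion of consenting eligible participants.

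Recruitment and procedure gives the order of events:

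- Consent and screening come first: "Researchers then invite potential participants to provide informed consent and to be screened for study eligibility".
- Baseline follows, and randomisation depends on it: "Eligible participants are then invited to complete the baseline assessment and, upon doing so, are randomised".
- Follow-up is limited to those randomised: "All randomised participants are invited to complete two post-allocation follow up assessments at 10 and 14 weeks".

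In the same list of parameters, the session criterion uses a post-randomisation denominator: at least "80% of participants allocated to receive G4H will complete at least four sessions". The Abstract names randomisation as a feasibility question separate from retention: "feasibility of recruitment, randomisation, data collection and retention to the study at 10 and 14 week follow up". The target under Sample size is stated in terms of the arms: "The trial aims to recruit 30 young adult participants, providing 15 participants in each trial arm".

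**The concern.** Three groups can be distinguished: people who consent and are found eligible, those among them who complete baseline and are randomised, and those among the randomised who are followed up. The retention parameter divides the third by the first. A person who consents, is eligible and does not complete baseline is never due a 10- or 14-week assessment, yet counts as not retained.

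The figure then combines two different losses: failure to reach randomisation, and loss to follow-up after it. A feasibility trial has reason to keep them apart because they point to different remedies. The combined figure also cannot be split by arm, since people who were never randomised have no arm. What is at stake is whether this one parameter is judged correctly against its 80% threshold.

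**Working it through.** There is no derived figure to reproduce. The 80% is a set threshold, the 30 is a target (15 + 15), and the article says that "a power calculation was not undertaken as the study focus is on feasibility goals". The check is what the threshold demands under each denominator.

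**Inputs**

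- Threshold: 0.80 at each follow-up (key feasibility parameters).
- Randomised: R = 30 (Sample size).
- Consenting eligible people lost before randomisation: L. The article gives no value, so L is varied.
- Retained is taken to mean followed up at the time point in question.

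**Formulas**

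- Number needed as written: N = 0.80 × (30 + L), rounded up to a whole person.
- Retention this requires among the randomised: N / 30.
- Chance of meeting the parameter at one time point: P(X ≥ N), with X binomial (30, p). True retention p among the randomised is an assumption; 0.85, 0.90 and 0.95 are shown.

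| L | 30 + L | 0.80 × (30 + L) | N | N / 30 | p = 0.85 | p = 0.90 | p = 0.95 |
|---|---|---|---|---|---|---|---|
| 0 | 30 | 24.0 | 24 | 80.0% | 0.847 | 0.974 | 0.999 |
| 1 | 31 | 24.8 | 25 | 83.3% | 0.711 | 0.927 | 0.997 |
| 2 | 32 | 25.6 | 26 | 86.7% | 0.524 | 0.825 | 0.984 |
| 3 | 33 | 26.4 | 27 | 90.0% | 0.322 | 0.647 | 0.939 |
| 4 | 34 | 27.2 | 28 | 93.3% | 0.151 | 0.411 | 0.812 |
| 5 | 35 | 28.0 | 28 | 93.3% | 0.151 | 0.411 | 0.812 |
| 6 | 36 | 28.8 | 29 | 96.7% | 0.048 | 0.184 | 0.554 |
| 7 | 37 | 29.6 | 30 | 100% | 0.008 | 0.042 | 0.215 |
| 8 | 38 | 30.4 | 31 | not attainable | 0 | 0 | 0 |

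**Worked cases**

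- L = 0: the denominators coincide, and 24/30 = 80.0% just meets the parameter.
- L = 1: the same 24 followed up give 24/31 = 77.4%, a miss.
- L = 4: 27 followed up is 27/30 = 90.0% of the randomised, but 27/34 = 79.4% as written, a miss.
- L = 8 (8/38 = 21% of those consenting and eligible): complete follow-up gives 30/38 = 78.9%, so the parameter cannot be met.

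**If 30 is instead the number consenting and eligible.** Then 24 are needed whatever happens before randomisation. Losing 3 before randomisation leaves 27 randomised and requires 24/27 = 88.9% of them; losing 6 requires 24/24.

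**With the randomised as denominator.** 24/30 is needed for every L, and the L = 0 row applies throughout.

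**The case against.** The best defence is that *consenting eligible* is shorthand for enrolled. Primary outcomes uses the same phrase for attendance at all five G4H sessions. Taken literally, that would put the control arm, which is not offered G4H, in the denominator. Sample size likewise treats recruiting 30 as equivalent to having 15 in each arm. This has some force and suggests loose wording more than a deliberate choice. It does not settle the matter. The article nowhere equates the two groups, its procedure separates them by a completed baseline assessment, and it uses *allocated* and *randomised* where it means those. On either reading the wording needs the same correction.

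Several stronger readings are tempting and are not supported:

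- **That the trial could fail on this.** The thresholds are feasibility parameters with no stop/go rule, and the Abstract and Introduction say that results will indicate whether further optimisation is needed.
- **That loss before randomisation would be hidden, and the team would repair the wrong step.** Analysis commits to reporting participant flow under the CONSORT extension for pilot and feasibility trials, so a reader could compute retention among the randomised.
- **That pre-randomisation loss will be large.** Nothing in the article suggests 8 in 38. Baseline carries a £20 voucher, is arranged at a time that suits the participant, and can be done with a researcher's help.
- **That the larger trial will take its attrition allowance from this figure.** That is a reasonable inference, but the article does not say it.
- **That the article is deficient because it lists no separate outcome for the step from eligible to randomised.** A condensed article may leave such detail to the full protocol, so this is not held against it.

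**Conclusion.** The point holds as a mismatch between a stated denominator and the article's own procedure. Followed as written, the parameter charges loss before randomisation to retention and can be missed despite adequate follow-up of those randomised.

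The size depends wholly on L. With no such loss there is no effect. With 30 randomised, each of the first four people lost raises the required number by one, so that at L = 4 the 80% threshold has become 93.3% of the randomised. At an assumed true retention of 90%, the chance of meeting it at one time point falls from 0.974 to 0.411 between L = 0 and L = 4. These figures assume the recruitment target is reached and that participants are independent.

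The consequence is a misjudged feasibility parameter, recoverable from the reported flow. It is worth correcting because the text as it stands can give the wrong answer on one of its key criteria, and correction is nearly free.

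**What to change.** Define retention, in both the primary outcome and the 80% parameter, as the proportion of randomised participants who complete the assessment at each follow-up time point, and report it overall and by arm. Alongside it, report the number and proportion of consenting eligible participants who are randomised, taken from the CONSORT flow counts.

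The cost is two lines of outcome wording and the usual notification of an amendment to the sponsor and ethics committee. No new data are needed: both counts are required for the flow diagram already, and the threshold itself need not change.
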